### Validation of the questionnaires

We will use available validated versions of the EPDS, GAD-7 and PTSD DSM-5 checklist in the official language of all the participating countries. However, COPE-IS, COPE-IU and COPE-CF are newly developed measures, and psychometric properties are yet to be established. Scoring procedures also need to be determined. The COPE questionnaires were originally available in English and translated to Spanish and German. Thus, researchers from each country involved in the study performed the translation and cultural adaptation of the questionnaires from English into the official language of their country, following several methodological steps, defined a priori, as detailed in Table 2. No major discrepancy was identified in any of the cross-cultural adaptations.

**Table 2 Tab2:** Cross cultural adaptation of the COPE questionnaires

• Adaptation of “demographic variables”	
• Forward and backward translation from the original version	
• A pilot study with a small (*N* ≥ 4) sample of pregnant women and new mothers (to assure comprehensibility of the items as intended)	
• Revision of the instrument by an expert committee (in the perinatal field) in each country (*N* ≥ 2 persons)	

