### Data collection

Participants will be recruited through social media advertising (Twitter, Facebook, Instagram, LinkedIn, ResearchGate, WhatsApp, etc.), networks of organizations (including universities, health centers, NGOs working in the field of perinatal mental health), policymakers, local organizations, and other stakeholders (using the network provided by the Riseup-PPD), as well as personal networks of colleagues and acquaintances of the research team members, and direct contact by mobile message or email.

Participants will be asked to click on the project website link (see the general project website: https://momsduringcovid.org) to be directed to the online questionnaire for their specific country. First, they will read an electronic consent form presenting an overview of the study aims, content of the questions asked, potential risks and benefits, and ethical aspects of the study (i.e., voluntary participation, confidentiality and secure storage of the data, and absence of any type of compensation). At the bottom of the form, they will be asked to confirm a set of eligibility criteria and to provide their consent to access the study. Participants who do not meet the predefined inclusion criteria will be directed to a message thanking them for their interest and informing them of the required eligibility criteria for participation in the study.

The baseline questionnaire is estimated to take approximately 20 min to complete. Eligible participants who complete the baseline questionnaire will be invited to provide their email or phone number to be contacted to participate in the three follow-up assessments. Participation in the follow-ups will be optional and participants will need to provide their consent to be contacted by email or phone (text messages only). Attached to this request, we will provide a clear plan to guarantee confidentiality and protection of the contact information provided (this information will also be provided in the Informed Consent).

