### Data analysis

Patterns of missingness in the data will be studied and the Expectation-Maximization algorithm will be implemented to impute missing data. Attrition analyses will be carried out to examine differences between participants who completed all the assessments and those who did not. Descriptive statistics will be examined for the study variables for all the assessment times. Measurement equivalence will be studied in order to ensure we are measuring the same variables across countries.

Changes in mental health between baseline and the follow-ups will be examined by testing latent growth curve models for each outcome. Moreover, the relationships between the rates of change in predictors (i.e., risk and protective factors) and mental health results during the follow-up will be analyzed. Multilevel analyses will be performed to control the moderation of demographic variables in those interrelations. Regarding the overall fit of these models, Satorra-Bentler χ^2^, CFI, RMSEA and the confidence interval for the RMSEA statistics will be calculated. Lagrange multipliers and the Wald test will be performed sequentially to improve the fitness of the models, following the hypotheses of the study. Standardized coefficients and measurement equations with scores in R^2^ will be reported. These analyses will be undertaken using the statistical program EQS. 6.3.

To determine the risk and protective factors to predict perinatal mental health outcomes during the COVID-19 pandemic, a random sample of 70% of the data will be used to derive the machine learning algorithms including regularized logistic regression, random forest, decision tree, and gradient boosting to predict the risk of PPD, and their performance, and the remaining 30% for validation. First, in the derivation sample, all the predictors described above will be entered into the models to estimate the probability of depression or anxiety or PTSD. Beginning with a model containing all potential covariates, the variable with the least significant *P* value will be removed and tested using the likelihood-ratio test until all variables left in the model significantly (at alpha = 0.05) contribute to the model.

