In regularized logistic regression models, results will be presented as odds ratio (OR) with 95% confidence intervals (CIs). The R^2^ will be used to calculate the proportion of the explained variance of clinical outcomes by the selected predictors. The different aspects of model performance will be studied, including calibration and discrimination. Calibration will be assessed using the Brier score and by plotting the non-parametric estimate of the association between the observed frequencies and the predicted probabilities. The receiver operating characteristic (ROC) curves (and the corresponding area under the ROC curve—AUC) will be calculated to test for discrimination. To correct optimism, internal validation will be performed for each model using the bootstrap procedure with 500 bootstrapped samples. The final models will be selected to derive scores for clinical use, and nomograms will be created. Criteria for this selection will include both discriminant ability (defined by the AUC) and model simplicity. Finally, the coefficients (scores) derived from the derivation cohort will also be validated in the validation cohort. These statistical analyses will be carried out in R and Python. The analyses will conform to the reporting standards of transparent reporting of a multivariable prediction model for individual prognosis or diagnosis (TRIPOD) [49].

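### Missing outcomes are not exempted from Expectation-Maximization imputation, so imputed follow-up scores could count as truth in the 30% validation sample

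*Protocol article*

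**What the plan says.** The Data analysis section of the protocol article opens with missing data: "the Expectation-Maximization algorithm will be implemented to impute missing data". The sentence is limited neither to predictors nor to any one analysis. Two paragraphs later, for the prediction models, "a random sample of 70% of the data will be used to derive the machine learning algorithms", with "the remaining 30% for validation". In the derivation part, "all the predictors described above will be entered into the models to estimate the probability of depression or anxiety or PTSD". AUC is one of the two criteria for choosing the final models, the Brier score and a calibration plot are the calibration measures, and the chosen models are to yield scores and nomograms for clinical use. As the last step, the derived scores "will also be validated in the validation cohort".

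Under Aim, the depression and anxiety events to be predicted are new cases above the cut-off during follow-up. The cut-offs are EPDS 13 or more and GAD-7 10 or more. Under Data collection, "Participation in the follow-ups will be optional", and a woman must also give contact details and consent to be contacted. No dropout rate is given.

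**The concern.** The events to be predicted lie in the part of the study most exposed to missing data. An unrestricted imputation rule reaches those outcomes. EM fills a missing follow-up score from the woman's other data, and those data include the variables that the prediction model uses. If such a woman is in the 30%, the model is credited for agreeing with a value computed partly from its own predictors.

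A second effect concerns the cut-off. If EM supplies the conditional mean, imputed scores vary too little and seldom reach 13 (EPDS) or 10 (GAD-7). Event rates then fall in the 70% and the 30% alike. The model learns risks that are too low, and the validation sample confirms them because it is too low in the same way. The bootstrap correction gives no protection if it resamples the same completed data.

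At stake is the last check before a score is offered for clinical use. It could report good accuracy and calibration for a score that understates risk.

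**Working it through.** **Inputs.** From the article: 70/30 random split; EPDS cut-off 13; 14 countries with at least 300 women each, so 14 × 300 = 4,200 as simulation size. The article gives no AUC, Brier score, dropout rate, predictor R² or EM variant, so there is no figure of the plan's own to reproduce. Everything below rests on assumed ranges for these.

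**Step 1: why conditional-mean imputation loses cases.** Take a normally distributed score with true prevalence p = 0.198, so the cut-off lies z = 0.849 SD above the mean. Conditional means have SD √R² times the score's SD, so the share of imputed women above the cut-off is 1 − Φ(z/√R²). With a fraction m missing, apparent prevalence = (1 − m)·p + m·[1 − Φ(z/√R²)].

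- R² = 0.30: 0.849/0.548 = 1.55, upper tail 0.061. At m = 0.4: 0.6 × 0.198 + 0.4 × 0.061 = 0.143. At m = 0.6: 0.4 × 0.198 + 0.6 × 0.061 = 0.116.
- R² = 0.15: 0.849/0.387 = 2.19, upper tail 0.014. At m = 0.6: 0.4 × 0.198 + 0.6 × 0.014 = 0.088.

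The simulation in Step 2 gives 0.143, 0.116 and 0.089.

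**Step 2: one follow-up outcome, all women.** 4,200 women, 15 predictors, ridge logistic model, 60 replicates, outcomes missing completely at random. Apparent = scored on the imputed outcomes; true = same model scored on the real outcomes.

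| R² | Missing | AUC apparent / true | Brier apparent / true |
|---|---|---|---|
| 0.30 | 20% | 0.782 / 0.768 | 0.116 / 0.135 |
| 0.30 | 40% | 0.808 / 0.770 | 0.094 / 0.136 |
| 0.30 | 60% | 0.834 / 0.768 | 0.074 / 0.143 |
| 0.45 | 60% | 0.903 / 0.835 | 0.067 / 0.125 |
| 0.15 | 60% | 0.706 / 0.685 | 0.075 / 0.162 |

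At R² = 0.15 with missingness depending on a predictor, apparent AUC falls below the truth: 0.675 v 0.686 at 20% missing and 0.670 v 0.679 at 40%. The largest AUC gap came from a similar simulation (20 predictors, 40 datasets) at R² = 0.35 and 70% missing: 0.897 − 0.785 = 0.112.

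**Step 3: does the order of imputation and split matter?** At R² = 0.30 and 40% missing, imputing the whole dataset gives AUC 0.808. Splitting first and fitting the imputation in the 70% only, while still filling in outcomes in the 30%, gives 0.807. The true value is 0.769 to 0.770. Across all settings the two orders differ by at most 0.005 in AUC and 0.001 in Brier score.

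**Step 4: closer to this plan's endpoint.** Baseline non-cases only, with baseline EPDS used in the imputation, R² = 0.35 and 50% missing. One run (residual correlation between waves assumed 0.6) gave AUC 0.734 v 0.723, Brier 0.057 v 0.101 and prevalence 0.064 v 0.118. Another run of this kind gave Brier 0.056 v 0.098, with mean predicted risk 0.065, imputed event rate 0.063 and true rate 0.115. Predicted risk thus matches the imputed rate, while the true rate is 0.115/0.065 = 1.8 times as high.

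Most of the Brier gap follows from the lost cases. A model that predicts only the base rate scores p(1 − p): 0.064 × 0.936 = 0.060 against 0.118 × 0.882 = 0.104.

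**Step 5: alternatives.** With a residual draw added to each imputed value, AUC is within about 0.01 of the truth and Brier within about 0.003. With observed outcomes only, missing completely at random, AUC is within about 0.006 of its no-missing value and Brier is also close. When missingness depends on a predictor, observed-only AUC stays within about 0.013, but Brier drifts low (0.119 v 0.135 at R² = 0.30, 60% missing), so weighting for response is needed.

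**The case against.** The strongest objection is that the article never says that outcomes are imputed, that imputation precedes the split, or that imputed outcomes are scored in the 30%. It is a condensed article, and such detail usually sits in an analysis plan that is not shown. This stands in part: a reader might infer from the sentence order that the split follows imputation of the whole dataset, and the text does not establish that. But a missing-data rule is stated here, without restriction, and following it literally reaches the outcomes. The point concerns a stated rule, not an omitted detail.

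Other stronger readings also go beyond the documents:

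- **Leakage through the order of steps.** Step 3 shows that order alone changes almost nothing.
- **AUC is certainly too high.** With new cases only and baseline EPDS in the imputation, the AUC gap shrinks to about 0 to 0.05. At R² = 0.10 it was 0.592 v 0.594. Weak predictors or residual draws remove most of it.
- **Rows of one woman on both sides of the split.** The split is described as of the data, but the same section then speaks of a derivation cohort and a validation cohort, which points to women.
- **COPE scores tuned on validation women.** The article says "Scoring procedures also need to be determined", but not that this dataset will be used to determine them.

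**Conclusion.** The concern holds in a conditional form. As written, the imputation rule allows follow-up EPDS and GAD-7 outcomes in the validation sample to be filled in and then treated as truth. Under conditional-mean imputation the firm consequences are a Brier score that is too low and a calibration check that confirms under-predicted risk. The Brier score was too low in every simulated setting of Step 2 with missing outcomes. The effect on AUC is less certain: an overstatement of about 0 to 0.11, with no change or a slight fall when predictors are weak.

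All sizes rest on assumed R², missingness, correlation between waves and EM variant. If the sponsor intends residual draws, or intends to leave outcomes unimputed in the prediction analysis, the bias is small or absent, and saying so would settle the point.

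**What to change.** State that singly imputed outcomes are not used in the prediction analysis. Specifically:

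- Compute AUC, Brier score and calibration in the 30% only among women with an observed follow-up outcome, weighted for response; or use proper multiple imputation with residual draws.
- Derive the model in the 70% on the same basis, so that its predicted risks are not pulled down.
- Fit the imputation of missing predictors in the 70% and apply it unchanged to the 30%.
- State that the split is by woman.

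This takes a few sentences in the analysis plan and no new data. The cost is fewer women in the validation sample, and a less favourable Brier score and usually AUC. Response weighting corrects only for the measured predictors of response, so the existing attrition analysis should be reported beside the validation results.

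### Score coefficients, and by the natural reading the odds ratios, come from a random 70% of the data with no stated refit on the full cohort, so the prediction-model part of primary objective 2 loses precision it could keep

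*Protocol article*

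**What the plan says.** Primary objective 2 (Aim) is to determine the risk and protective factors that predict perinatal mental health outcomes. The Data analysis section takes up that objective and ties it to a random split: "a random sample of 70% of the data will be used to derive the machine learning algorithms", and "the remaining 30% for validation".

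The model building is placed in the larger part: "First, in the derivation sample, all the predictors described above will be entered into the models". Backward elimination then runs "until all variables left in the model significantly (at alpha = 0.05) contribute to the model". For the regularized logistic models, "results will be presented as odds ratio (OR) with 95% confidence intervals (CIs"); the sentence does not say in which sample. Final models are chosen on AUC and simplicity and turned into clinical scores and nomograms. As a last step, "the coefficients (scores) derived from the derivation cohort will also be validated in the validation cohort".

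The same section also provides for optimism correction: "internal validation will be performed for each model using the bootstrap procedure with 500 bootstrapped samples". No sentence says that the chosen model is refitted on the whole cohort.

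**The concern.** One split serves two purposes. Measuring how well a model predicts is a proper use of a hold-out. Estimating an odds ratio and its confidence interval, or fixing the coefficients of a score, does not need one, and those estimates are better with all the data.

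As written, the held-out women check the score but do not contribute to the coefficients that will be published. Precision is lost on a primary objective. Because predictors are kept or dropped by P value, the list of factors declared relevant also rests on fewer women and on one random draw. For depression and anxiety the outcome in objective 2 is new cases during follow-up, and follow-up is optional (Data collection), so the women who inform this analysis may be well below the number enrolled.

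**Working it through.** **Inputs from the protocol article.** Derivation share 0.70 and hold-out share 0.30 (Data analysis); elimination at alpha 0.05 (Data analysis); minimum 300 women per country (Sample size); 11 + 3 = 14 countries (Setting). Planned minimum: 14 × 300 = 4,200 women, split into 0.7 × 4,200 = 2,940 and 0.3 × 4,200 = 1,260.

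**The plan's own figure.** The 300 per country cannot be reproduced, because no margin of error is given. With a proportion of 50% and two-sided alpha 0.05, a 5% margin gives 385; 300 corresponds to a margin of 1.96 × sqrt(0.25/300) = 5.66%. Nothing below depends on this except the total of 4,200.

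**Step 1: standard errors.** For a prespecified, unpenalised model, information is proportional to the number of women. The ratio of standard errors, 70% fit to full fit, is 1/sqrt(0.7) = 1.195, and the variance ratio is 1/0.7 = 1.43. Confidence intervals on the log odds ratio are about 20% wider at any sample size.

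**Step 2: power.** Power at 70% of the information = Φ((1.96 + z_power) × sqrt(0.7) − 1.96).
- 80% on all data: (1.96 + 0.84) × 0.837 = 2.34; Φ(0.38) = 65%.
- 90% on all data: (1.96 + 1.28) × 0.837 = 2.71; Φ(0.75) = 77%.

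**Step 3: detectable odds ratio.** Assumptions, not in the document: overall case risk 15%, factor present in 20% of women. Solve ln(OR) = (1.96 + 0.84) × SE, where SE is the Wald standard error of the log odds ratio from the 2 × 2 table, for 80% power.

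| Women available | Full-cohort fit | 70% fit |
|---|---|---|
| 4,200 (all of the planned minimum) | 1.33 | 1.40 (n = 2,940) |
| 2,100 (half retained, assumed) | 1.49 | 1.60 (n = 1,470) |
| 10,000 (assumed larger enrolment) | 1.21 | 1.25 (n = 7,000) |

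**Step 4: check by simulation.** Unpenalised logistic regression with 4,200 women, five binary predictors each with assumed 20% prevalence, 1,000 runs. Ratios of standard errors were 1.195 to 1.198. Power fell from 0.79 to 0.62 for an odds ratio of 1.3 and from 0.45 to 0.36 for 1.2.

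**The case against.** The strongest case on the other side has four parts.

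- **The sample for the odds ratios is not named.** A reader might infer that the plan says outright that the odds ratios use only the 70%. It does not. That follows from the models being built in the derivation sample and from the coefficients being described as derived there, an odds ratio being an exponentiated coefficient. For the score, the source is explicit. A condensed article might also leave a final refit to a fuller document, but this one sets out the split, the fitting sample, the elimination rule and the source of the coefficients, and the sequence ends without a refit.
- **The hold-out has a use.** It would be too strong to say that the 30% is wasted. Predictors are chosen by P value and final models by AUC and simplicity, so data not used in those choices give a useful check. This stands, and it is why the split should stay for performance. But a random 30% of the same cohort is still internal validation, and the check does not require the published estimates to be confined to the other 70%.
- **Other analyses address risk factors.** A reader might infer that the whole risk-factor question rests on the 70%. The latent growth and multilevel models relate changes in predictors to outcomes and carry no stated split. They produce neither the odds ratios nor the score, so the point is limited to the prediction models.
- **The arithmetic is approximate.** With penalisation and stepwise elimination, standard errors do not follow the simple formula exactly, and 95% intervals are not nominal at either sample size. The 4,200 is a floor, since enrolment is not restricted. This stands.

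**Conclusion.** The point holds as a loss of efficiency in the prediction-model part of primary objective 2. It is not an invalid analysis, nor is a bias created by the split. Followed as written, the plan gives standard errors about 1.2 times those of a full-cohort fit, with power of 80% falling to about 65% and 90% to about 77%. These relative figures need no assumption about recruitment, but they are exact only for an unpenalised, prespecified model. The absolute effect is modest at the planned minimum and depends on the assumed risk, exposure and retention: it grows with attrition and shrinks with larger enrolment. The change is worth making because it is cheap and the hold-out check can be kept.

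**What to change.** Keep the 70/30 split to report prediction performance. Then state that, once the procedure has been selected and checked, it is refitted on all eligible women, and that the odds ratios, confidence intervals, score and nomogram come from that refit. Specify that the planned bootstrap repeats every selection and tuning step in each resample, so that it gives optimism-corrected performance for the full-data model.

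The cost is a few sentences, one further model fit, and a bootstrap run on the full-data procedure; no new data are needed. There are two limits to disclose. The published coefficients will not be the literal ones tested in the 30%, so both sets should be distinguishable in the report. And the refit does not remove the selection bias that comes from backward elimination by P value.

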We hypothesize an increase in negative perinatal mental health outcomes (symptoms and clinical risk) among women during the COVID-19 pandemic. We also hypothesize that common risk factors (e.g., low income, low social support, high level of psychological distress, previous history of mental disorders) will be associated with an increase in the clinical risk of depression and anxiety during the COVID-19 pandemic. Additionally, we hypothesize that pandemic-related risk factors, such as being exposed to and/or having a positive diagnosis for COVID-19, will be associated with increased risk of perinatal mental disorders.

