##### COVID-19 exposures and symptoms

Six items about (1) the diagnosis of COVID-19; (2) any symptoms compatible with the coronavirus disease; (3) contact with someone who has been diagnosed with COVID-19; (4) any death of family or friends due to COVID-19; (5) the level of distress about COVID-19-related symptoms or potential illness: (5a) their own illness or (5b) in their friends and family [31, 32].

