##### COVID-19 emotional impact

Four items assessing the subjective impact of the COVID-19 pandemic. The questions include: (1) overall level of impact on daily life due to the COVID-19 pandemic; (2) overall level of stress related to the COVID-19 outbreak; (3) perceived positive or negative impact of the COVID-19 pandemic; and (4) how long participants think it will take for things to go “back to normal”? [31, 32].

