#### Brief symptom Inventory-18

The Brief Symptom Inventory-18 (BSI-18), omitting suicidality, will be used to evaluate psychological distress [34] in the last week. The BSI-18 is an 18-item self-report questionnaire which includes a summary scale of overall distress, the Global Severity Index (GSI), and three subscales: depression, anxiety, and somatization. Each item is rated on a 5-point scale, with distress ratings ranging from 0 (not at all) to 4 (extremely). For the purposes of the current study, only the GSI will be examined. The GSI level is the summed score of all the items [34].

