### Significance and practical implications of the study

A previous position paper highlights that an immediate public health priority is evidence-based research on the mental health effects of the COVID-19 pandemic in vulnerable populations [22], such as women during the perinatal period [11]. Furthermore, there is an urgent need for research to address how to mitigate the mental health consequences of COVID-19 in women during the perinatal period [22].

The findings will provide critical information regarding the risk and protective factors for perinatal mental health disorders during the COVID-19 pandemic. The results of this study will offer clarification on the impact of the pandemic on women during the perinatal period, allowing the development of comprehensive models for the prediction of perinatal mental disorders, specifying the contribution of each risk and protective factor and contributing to the design of tailored interventions to support women during the COVID-19 pandemic. This will allow perinatal healthcare providers to assess women at risk of developing mental health disorders during the pandemic and provide early intervention as well as develop preventive measures. In addition, the findings of the study will assist policymakers and healthcare providers in developing guidelines and preventive interventions for perinatal mental disorders in future pandemics.

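### The main risk-factor procedure judges COVID-19 exposure and diagnosis net of distress that may follow from them, so it does not answer the stated exposure hypothesis

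*Protocol article*

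**What the plan says.** All places are in the protocol article.

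- **Aim (hypotheses).** The third hypothesis concerns factors tied to the pandemic: "being exposed to and/or having a positive diagnosis for COVID-19, will be associated with increased risk of perinatal mental disorders". It is an overall association; nothing says it is net of distress. A secondary objective also compares the risk in COVID-19-positive women with that in other women.
- **Background.** Fear of infection and transmission, isolation and changed maternity care are named as things that may raise psychological distress.
- **Predictors (Table 1 and the measure descriptions).** One six-item block holds diagnosis, symptoms, contact and bereavement together with "the level of distress about COVID-19-related symptoms or potential illness". The emotional-impact block includes "overall level of stress related to the COVID-19 outbreak". Coping strategies are a further block. The BSI-18 is listed as a predictor and "will be used to evaluate psychological distress [34] in the last week".
- **Data analysis.** The paragraph on determining risk and protective factors says that "all the predictors described above will be entered into the models to estimate the probability of depression or anxiety or PTSD". The least significant variable is then removed by likelihood-ratio test, and so on "until all variables left in the model significantly (at alpha = 0.05) contribute to the model". Odds ratios with confidence intervals are to be reported. An earlier paragraph plans latent growth curve models that relate rates of change in predictors to outcomes.
- **Significance and practical implications.** The models are also meant for interpretation, "specifying the contribution of each risk and protective factor".

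**The concern.** A likelihood-ratio test of diagnosis or contact in the full model asks whether the exposure adds anything once distress, COVID-19 stress and coping are known. The hypothesis asks whether exposed women are at higher risk. The two questions agree only if little of the effect runs through distress, and the article itself treats distress as a likely consequence of the pandemic.

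If most of the effect takes that route, elimination drops the exposure, and it may then be reported as not a risk factor although the same data could show that it is one. The third hypothesis and the positive versus non-positive comparison are both exposed to this. So is the promised account of what each factor contributes, which is meant to inform interventions and policy.

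**Working it through.** **Sample size.** The article gives a minimum of 300 women in each of 14 countries and a 70% derivation sample: 14 × 300 = 4,200, and 0.7 × 4,200 = 2,940. The plan states no power or effect size for this hypothesis, so there is no figure of its own to reproduce.

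**Assumed inputs (none is in the article).** Exposure E is present in 10% of women. Distress is D = d·E + noise with SD 1. Latent symptoms are L = c·E + 0.6·D + noise, and a woman is above the cut-off when L > 0.84, which is about 20% of the unexposed. The mediated share is 0.6d / (0.6d + c):

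- d = 0.4, c = 0: 0.24 / 0.24 = 100%
- d = 0.4, c = 0.08: 0.24 / 0.32 = 75%
- d = 0.3, c = 0.18: 0.18 / 0.36 = 50%

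**Test.** Logistic likelihood-ratio test of E at 0.05, counted when significant in the harmful direction, without and with D in the model; 600 runs per scenario.

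| Mediated share | OR without D | OR with D | Detected without D | Detected with D |
|---|---|---|---|---|
| 100% | 1.50 | 1.0 | 82% | 2% |
| 75% | 1.73 | 1.19 | 97% | 21% |
| 50% | 1.84 | 1.47 | 99% | 71% |

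Repeat runs agree to within a few points (80% versus 2%; 95% versus 21%; about 100% versus 70%). The 2% is simply the harmful half of a 5% test when nothing is left to detect.

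**Sensitivity (detected without versus with D).**

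- n = 1,470 (assumed 50% retention): 49% versus 2%, 76% versus 13%, 86% versus 39%.
- 5% exposed, n = 2,940: 54% versus 2%, 81% versus 14%, 88% versus 40%.
- 20% exposed, n = 2,940: 96% versus 1%, 100% versus 27%, 100% versus 92%. The last is a loss of about 8 points.
- About 30% mediated, 10% exposed: about 100% versus 98% where power is at its ceiling. Holding the total latent effect at 0.36, as in the 50% row (d = 0.18, c = 0.252; 0.108 / 0.36 = 30%), a rerun gave 99% versus 93%. So the small loss at low mediation relies on a strong total effect.

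**A differently built model** (logistic outcome, 20% risk, 10% exposed, n = 2,940) gives the same pattern. Wholly mediated: OR 1.59 becomes 1.01, retained in 88% versus 3%. Mostly mediated: 1.70 becomes 1.19, 93% versus 14%. Larger direct effect: 1.81 becomes 1.44, 98% versus 60%.

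**Sign reversal.** This needs a further assumption. With full mediation (slope 0.5) and an unmeasured cause shared by distress and symptoms that makes up 40% of the variance of distress, the exposure is detected in 64% versus 0%. The conditional OR is about 0.81, significantly protective in 21% of runs.

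**The case against.** **It is a prediction model.** It is to be assessed by AUC, Brier score, calibration and bootstrap, and reported under TRIPOD. Mediators are legitimate predictors, and the Aim section lists high distress as a hypothesised risk factor in its own right. This stands: including distress is no error for prediction. It does not cover the interpretive use, because the same procedure is introduced as the way to determine risk factors.

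**Other analyses are planned.** A reader might infer that the exposure hypothesis has no other analysis at all. The article does not support that. The growth curve models concern predictors described as risk and protective factors, and their refinement is to follow the study hypotheses. They relate rates of change in predictors to outcomes, however, and are not described as comparing exposed with unexposed women overall.

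**Timing.** Exposure is recorded at all four assessments, and the article does not say which assessment supplies the predictors. For an exposure that arises during follow-up, baseline BSI-18 comes first and may be a confounder to adjust for. This stands and limits the point to exposures that precede the distress measure. A diagnosis or death already reported at baseline generally precedes last-week distress at baseline, so using only baseline scores does not remove the problem for those women.

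**A condensed article.** A separate exposure model may sit in an unseen analysis plan, and its absence here is not the finding. The finding is that a stated predictor set and elimination rule do not match a stated hypothesis.

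**Assumed magnitudes.** Every effect input is assumed. The simulation uses two variables, not the full elimination, and ignores the restriction to new cases. This stands; the figures show what can happen, not what will.

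**Conclusion.** The mismatch is in the text and does not depend on the simulation. For exposures that precede the distress, stress and coping measures, the stated procedure gives an association conditional on them, while the hypothesis and the positive versus non-positive comparison concern the overall association.

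How much is lost depends on the share of the effect that runs through distress, on how common exposure is, and on the strength of the total effect. Under the inputs above, the loss ranges from about 78 points when fully mediated (80% to 2%) to about 29 points when half is (99% to 70%). It shrinks to about 8 points at 20% prevalence with half mediated, and is negligible at about 30% mediation if the total effect is strong.

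A reader might go further and infer that the plan will remove or reverse a real exposure effect. The article does not support that: near-certain removal needs most of the effect to be mediated, and reversal also needs an unmeasured shared cause. Nor does the point rest on overlap between BSI-18 items and the outcome scales. The plan should be changed, because a named hypothesis could be answered wrongly from data that could answer it properly.

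**What to change.** Keep the all-predictor models for prediction and nomograms only, and state that elimination from them is not evidence that an exposure is not a risk factor.

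For the exposure hypothesis and the positive versus non-positive comparison, fit a separate logistic model for diagnosis and for contact, for each outcome, without elimination. For post-traumatic stress, use the outcome definition of the prediction model.

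- **Adjust for** variables that precede exposure: country, calendar date, perinatal stage, demographics, parity and history of mental disorder. Add baseline BSI-18 only where the exposure arises after baseline.
- **Leave out** distress, emotional-impact and coping items measured at or after the exposure.
- **Treat as exploratory** the other exposures: bereavement, financial impact and restrictions.
- **Label** any exposure estimate adjusted for later distress as a direct-effect (mediation) analysis.

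The cost is wording and a few regressions on data already being collected: two exposures by three outcomes is six main models. No new data or extra women are needed. The downside is two sets of odds ratios, which must be reported apart and clearly labelled.
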